**Other Outcomes**		
Mortality incidence	Number of participants that evolved to death (all cause mortality)	24
Non-serious adverse events occurrence	Number of participants experiencing at least one non-serious adverse event	1, 3, 6, 9, 12, 18, 24
**Subgroup analysis**	Age, gender, region of lesion, occurrence of SAS, frequency and type of epileptic seizures, presence of APOEε4, educational level.	

The data analysis is based on comparisons between biperiden x placebo groups considering the end of follow up or run-in periods. PTE post-traumatic epilepsy; EEG electroencephalography; mRS modified Rankin scale. SAS symptomatic acute seizures; APOEε4 polymorphic ε4 allele of the apolipoprotein E gene.

As primary outcome, we will investigate the number of participants with unprovoked seizures, counted starting 7 days after TBI until the two years follow-up period. The presence of seizures will be clinically confirmed by a neurologist to indicate PTE. Also, as a primary outcome, the number of patients experiencing at least one serious adverse event in the two years follow-up period will be compared between placebo and biperiden groups. The ICH Guideline for Clinical Safety Data Management: Definitions and Standards for Expedited Reporting defines serious adverse event as: “A serious adverse event (experience) or reaction is any untoward medical occurrence that at any dose: results in death, is life-threatening (NOTE: The term "life-threatening" in the definition of "serious" refers to an event in which the patient was at risk of death at the time of the event; it does not refer to an event which hypothetically might have caused death if it were more severe); requires inpatient hospitalization or prolongation of existing hospitalization, results in persistent or significant disability/incapacity, or is a congenital anomaly/birth defect” [19].

For secondary outcomes, it will be considered the frequency and type of clinical seizures at each specific timepoint during the two years follow up. Also, the number of participants presenting epileptiform discharges and electrographic seizures on the electroencephalogram recording will also be analyzed. For the neuropsychological status participants will be categorized according to the specific percentile rank defined for each cited standard test. Five health-related quality of life domains (mobility, usual care, usual activities, pain/discomfort, anxiety/depression) will be covered and compared between groups according to specific and total scores.

Other outcomes include the mortality incidence and occurrence of non-serious adverse events during the two year protocol.

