## Abstract

**Background:**

Traumatic brain injury (TBI) is one of the most important causes of acquired structural epilepsy, post-traumatic epilepsy (PTE), however, efficient preventative measures and treatment are still not available to patients. Preclinical studies indicated biperiden, an anticholinergic drug, as a potential drug to modify the epileptogenic process. The main objective of this clinical trial is to evaluate the efficacy of biperiden as an antiepileptogenic agent in patients that suffered TBI.

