### Participants

The study will enroll adults (18 to 75 years) of both sex who fulfill the following inclusion criteria: meet the moderate or severe TBI criteria according with the Glasgow Coma Scale (GCS) [15], in such a way that GCS is between 6 and 12 at the accident scene and/or between 3 (if sedated) and 12 at hospital admission; have computerized tomography (CT) scan with evidence of acute intraparenchymal hemorrhage and/or contusion; able to receive the first dose of treatment or placebo within 12 hours of brain injury, regardless of the accident cause. Participants, or their relatives in the event of patient´s unconsciousness, will have to provide written informed consent within 48 hours from the beginning of the protocol. Exclusion criteria are: current use of biperiden or antiseizure drugs; history of epilepsy, presence of other conditions that could increase risk factors for epilepsy development, such as perinatal injuries, meningitis, encephalitis, neoplasia, acute stroke, neurodegenerative diseases; any condition precluding the use of biperiden such as pregnancy, glaucoma, benign prostatic hyperplasia, atrioventricular block or cardiac arrhythmias; megacolon or mechanical obstruction of the gastrointestinal tract and inability to perform follow-up visits (e.g. homeless patients); refusal to participate in the study and current enrollment in other clinical trial. Alcohol intoxication or other psychotropic drug use at hospital admission will not lead to protocol exclusion.

We intend to recruit participants with acute TBI from at least ten hospitals located at different regions from Brazil (North, South, Southeast, Midwest and Northeast). After a first screening at the emergency care unit (ECU) for confirming eligibility criteria (which requires standard CT scan for acute TBI cases, electrocardiogram and pregnancy test for safety), those who fulfill all criteria will be included in the study. Because the emergency scenario and the injury severity, when the participant is not able to inform his medical history and is not accompanied by an appropriate informant, consent to participate and exclusion criteria might be confirmed within two days of protocol beginning. Participants will be prospectively monitored at their respective neurology/neurosurgery centers.

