### Interventions

Within 12 h after TBI, participants will receive intravenous (i.v.) infusions of 5 mg of biperiden (1 mL; Cinetol, Cristália, Brazil) diluted in 100 mL of 0.9% saline (treatment group) or 1 mL of sterile vehicle (sodium lactate, lactic acid, sodium hydroxide and water for injections) diluted in 100 mL of 0,9% saline (placebo group), every 6 hours for 10 days after TBI, until completing 40 total doses.

Patients will receive all standard of care treatment indicated for their clinical condition according to the hospital protocol and will not be deprived of any other required treatment, including all types of anti-seizure drugs, because of their participation in this study, regardless of the randomization group (placebo or biperiden) or the protocol period (intervention or follow up). Patients can be discontinued from the protocol if they remove the consent to participate; in any health conditions that health care providers, with sponsor agreement, believe that it is to the advantage of the patient not to comply with the procedures specified in this protocol; in case of screening error when including patients with history of epilepsy predicted in the study exclusion criteria (when this finding cannot occur at the time of recruitment).

During the hospitalization period, blood samples will be collected to analyze the genetic profile of patients regarding the presence of the polymorphic ε4 allele of the apolipoprotein E gene (APOEε4). Laboratory analyses will be performed by a central laboratory (DASA, São Paulo, Brazil), which is accredited by the College of American Pathologists (CAP, Northfield, IL, USA). Additional patients’ information, such as occurrence of adverse events, sociodemographic data, occurrence of symptomatic acute seizures, unprovoked epileptic seizures starting 7 days after TBI and clinical evolution will be collected during the hospitalization period. Suspected and diagnosed severe adverse events will be reviewed and adjudicated by the Ethics Committee and the external Data Monitoring Committee.

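### The primary count of post-traumatic epilepsy opens about three days before study drug ends, and the primary analysis as written does not separate those days

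*Protocol article*

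**What the plan says.** All references are to the protocol article.

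- **Aim** (Abstract, Background): "evaluate the efficacy of biperiden as an antiepileptogenic agent in patients that suffered TBI".
- **Primary efficacy outcome** (Outcomes, text below Table 1): "number of participants with unprovoked seizures, counted starting 7 days after TBI until the two years follow-up period". The safeguard stated there is: "The presence of seizures will be clinically confirmed by a neurologist to indicate PTE".
- **Treatment course** (Interventions): infusions "every 6 hours for 10 days after TBI, until completing 40 total doses". Under Participants, eligible patients must be "able to receive the first dose of treatment or placebo within 12 hours of brain injury".
- **In-hospital recording** (Interventions): "unprovoked epileptic seizures starting 7 days after TBI and clinical evolution will be collected during the hospitalization period". After discharge, a seizure diary takes over (Follow-up).
- **Secondary seizure outcomes** (Table 1 and the text below it): "it will be considered the frequency and type of clinical seizures at each specific timepoint during the two years follow up". The earliest timepoint is month 1.
- **Primary analysis** (Statistical analysis): a logistic regression adjusted for age and sex, giving one odds ratio.

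The article states no off-treatment condition for the seizure count and no analysis limited to the period after dosing.

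**The concern.** An antiepileptogenic claim concerns what remains once a short treatment has stopped. The outcome should then measure seizures that arise when the drug is no longer acting. Here counting begins while infusions are still running.

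The outcome is a yes/no status at 24 months, so one confirmed unprovoked seizure on day 8 weighs the same as epilepsy that appears at month 18. If the drug merely suppresses seizures while it is being infused, some patients whose only qualifying seizure would have fallen in those days drop out of the biperiden count. They then appear as epilepsy prevented, although nothing about epileptogenesis has changed.

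There may also be some misclassification in the other direction. A seizure related to the drug or to its cessation could be judged unprovoked by an assessor who does not know the allocation. That is a possibility only, since the definition is meant to exclude such events.

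What is at stake is the interpretation of a positive result as disease modification, more than whether a difference is found.

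**Working it through.** **Step 1. Overlap in time.** Inputs: 40 doses, 6-hour spacing, first dose at hour *s* after injury with *s* between 0 and 12, count opening at 7 × 24 = 168 h. Dose *k* + 1 is given at *s* + 6*k* hours, *k* = 0 to 39.

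- *s* = 0: last dose at 39 × 6 = 234 h (day 9.75). Doses with 6*k* ≥ 168 are *k* = 28 to 39, so 12 doses lie in the window.
- *s* = 12: last dose at 12 + 234 = 246 h (day 10.25). Doses with 12 + 6*k* ≥ 168 are *k* = 26 to 39, so 14 doses lie in the window.
- Overlap up to the last dose: 234 − 168 = 66 h to 246 − 168 = 78 h, or 2.75 to 3.25 days. Adding the last 6-hour interval gives 3.0 to 3.5 days.
- Counting window: about 730 − 7 = 723 days. The overlap is 2.75/723 = 0.4% to 3.5/723 = 0.5% of it.

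**Step 2. A placebo rate to work with.** The article states no placebo rate for its sample size. The stated 156 per group can be reproduced with an assumed 25% versus 10%, two-sided alpha 0.05 and 90% power:

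*n* = [0.25 × 0.75 + 0.10 × 0.90] × (1.96 + 1.2816)² / 0.15² = 0.2775 × 10.507 / 0.0225 = 129.6, rounded up to 130; 130 × 1.2 = 156.

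This makes 25% a plausible reading, not a stated one. The point made here does not affect the sample size. Evaluable patients per arm after 20% dropout: 156 × 0.8 ≈ 125, so 125 × 0.25 = 31.25 placebo cases.

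**Step 3. Possible size.** Let *f* be the share of placebo cases that qualify only through a seizure in the on-treatment days. The article gives no seizure timing, so *f* is assumed. Take no antiepileptogenic effect and complete suppression on drug. The observed biperiden rate is then 0.25 × (1 − *f*) and the spurious difference is 0.25 × *f*. The last column is the chance of a significant result favouring drug, from an unadjusted two-proportion normal approximation with 125 per arm; its nominal value is 2.5%.

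| *f* | Patients per arm | Difference (points) | Odds ratio | Chance of significance |
|---|---|---|---|---|
| 3/723 = 0.4% (even timing) | 0.1 | 0.1 | 0.99 | 2.6% |
| 5% | 1.6 | 1.25 | 0.93 | 4.2% |
| 10% | 3.1 | 2.5 | 0.87 | 6.7% |
| 20% (extreme) | 6.3 | 5.0 | 0.75 | 15.5% |

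Worked line for *f* = 10%: 0.25 × 0.90 = 0.225; difference 0.025; odds ratio (0.225/0.775) / (0.25/0.75) = 0.290/0.333 = 0.87.

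With placebo rates from 10% to 27%, *f* = 5–10% gives 0.5 to 2.7 points (0.10 × 0.05 = 0.5 points; 0.27 × 0.10 = 2.7 points).

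**Step 4. Do the secondary outcomes isolate those days?** Read cumulatively, every timepoint from month 1 onward contains days 7 to 10. Read as seizures per interval, the later visits exclude them. The article does not say which reading applies.

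**The case against.** **Only confirmed unprovoked seizures count.** This stands. A reader might infer that any seizure on drug, or one provoked by the drug or its withdrawal, becomes epilepsy by definition. The Outcomes section does not support that; only misclassification remains possible. Confirmation does not, however, recover a seizure that the drug suppressed.

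**The two effects can be separated.** A reader might infer that they cannot be told apart at all. That is too strong. Seizures are recorded in hospital from day 7 and by diary afterwards, and more than 99% of the window lies after dosing. An off-treatment count looks feasible.

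**An extra analysis belongs in the statistical analysis plan.** This is partly right. That plan is not at hand and may already contain such an analysis, in which case the fix is met. But the overlap does not arise from a missing analysis. It follows from an outcome window and a treatment period that the article itself fixes.

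**The size is small and assumed.** This also stands. The 12 to 14 doses inside the window are 30–35% of all doses, but that fraction says nothing about bias. A patient whose early seizure is suppressed but who has a later one is still a case, so only patients with no other qualifying seizure can shift the result. Nor does the article state an acute anticonvulsant action of biperiden in humans.

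**Day 7 should not be moved.** Replacing it as the primary start would discard genuine early-onset cases unless their seizures recur. That trade-off is debatable, so the day-7 primary count is better left in place.

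**The dosing wording.** A reader might see a conflict between the 10-day period and the 40 doses, since a first dose at hour 12 puts dose 40 at hour 246. But 40 × 6 h = 240 h is exactly 10 days of dosing, and the text lets the dose count close the course. No contradiction needs resolving.

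**Conclusion.** The point holds in a limited form. For a patient who completes dosing, the primary count includes about 2.75 to 3.5 days on treatment, and the primary analysis as written does not separate an acute on-drug effect from the antiepileptogenic one. The timing follows directly from the article and rests on no assumption beyond on-schedule dosing.

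The consequence cannot be sized from the article. It is negligible if seizures are spread evenly. It reaches at most about 1.25–2.5 points if 5–10% of placebo cases qualified only in that stretch, with a 25% placebo rate and complete suppression, all of which are assumed. That ceiling is at most one-sixth of the planned difference (2.5/15), and even the extreme 20% row gives only one-third (5/15). The overlap could therefore not produce the planned effect by itself within this range. It could bias the odds ratio and blur what a modest positive result means.

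The change is advisable because it bears directly on the trial's central claim and costs little. The overlap does not invalidate the primary outcome.

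**What to change.** 1. Keep the day-7 count as the primary outcome.
2. Pre-specify a supportive analysis that counts unprovoked, neurologist-confirmed seizures only from one fixed day after injury. Use the same day in both arms and for every patient, whatever number of doses was received, so that the randomised comparison is preserved. Set it after the latest scheduled last dose (hour 246) plus a washout that the sponsor justifies. A patient with seizures only before that day stays in the analysis as a non-case; one with a further unprovoked seizure afterwards is a case.
3. Report seizures between day 7 and that day separately by arm.
4. State in advance that an antiepileptogenic effect is concluded only if the two counts agree, and say what agreement means, for instance odds ratios in the same direction and of similar size.
5. Say whether the visit-level seizure outcomes are cumulative or per interval.

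Cost: one additional analysis of data already being collected, with slightly fewer events. At 125 per arm and 25% versus 10%, if both arms lost 5–10% of their cases, power for the supportive count would fall from about 88% to 86–84% on the same approximation. No change to treatment, visits or sample size is needed.

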### Statistical analysis

The statistic plan followed the Guidelines for the Content of Statistical Analysis Plan in Clinical Trials [20].

Sample size calculation was performed based on previous studies [1, 2, 5–8, 10, 21] using the Pocock formula [22]. Assuming a difference in reduction of PTE of 15% between the placebo and biperiden groups at 24 months, type 1 error (alpha) of 0,05 and type 2 error (beta) of 0.10 and 20% dropout rate, 156 patients per group would be required to provide 90% power with 5% level of significance. According to epidemiological data provided by a pilot study [10], we estimated that the inclusion pace could be 3–5 patients/center/month leading to study completion within 42 months.

The hypothesis used in the analysis is that biperiden is superior to placebo. All patients who receive at least one dose of randomized study drug will be included into the safety analysis and all patients who receive at least one dose of a randomized study drug and who has an evaluable follow-up data will be included in intention-to-treat analysis. Missing data will be handled by chained-equation multiple imputation methods considering relevant baseline and outcome variables. A complete case analysis will be presented as a sensitivity analysis.

We plan to analyze the primary outcome using logistic regression, adjusting for age and sex at baseline. The result of this regression will be an odds ratio representing the relative effect of the intervention compared to the placebo. Secondary outcomes will be analyzed using appropriate generalized linear models, including logistic and linear models. Planned subgroups include type of epileptic seizures and the presence of the polymorphic ε4 allele of the apolipoprotein E gene (Table 1).

An interim analysis will be performed at 50% recruitment considering the primary outcomes. At the interim enrollment point, the DMC will consider as criteria for early interruption of the study p<0.001 for safety and p<0.0001 for efficacy analysis. The Pocock [22] stopping boundaries, will be used as a reference rather than as a rigid rule. In addition, the DMC will also consider the effect on other secondary outcomes, in the occurrence of unpredicted adverse events and external new evidence available during trial conduction.

A confidence level of 95% will be assumed for all analyses that will be conducted using Stata v17.

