Because treatment has to be administered soon after injury, and because severe trauma patients may be unconscious and not accompanied by a legal responsible person at the hospital admission, research ethics committees from all study centers allowed an extended deadline of 48h to obtain the informed consent to the study after beginning treatment, in order to guarantee effective enrollment rate. Also, because some aspects of the clinic history may not be readily available during enrollment, some inclusion and exclusion criteria will be checked over the initial course of treatment, which may result in high exclusion rate of patients. In that case, data from those patients will be considered only for safety analysis.

The dose of intravenous injection of biperiden is similar to the maximum recommended dose to initiate treatment of severe cases of parkinsonism [25] and also showed to be safe in critical TBI patients [10]. However, severely injured patients receive a variety of treatments and drug interventions and, in addition to the evolution of the clinical condition, all those are confounding factors that must be taken in account when registering adverse effects that might be caused by the biperiden treatment. We will focus the analysis of adverse effects on the symptoms already described for biperiden without underestimating additional unreported occurrences, mainly during treatment, and its correlation with other possible causes.

The long-term assessments in different areas (EEG, neuropsychology, etc) will be conduct by specialized staff (neurologists, neurophysiologists, trained psychologists). To decrease loss of data associated to absence of the patient in presential visits on specified time points, e.g because social restrictions due COVID-19 pandemic or other reasons, essential data related to clinical evaluation of seizures development will be collected by phone calls, as necessary. Different contact options, such as relatives phone numbers and e-mail addresses will be collected and only after many frustrated attempts of contact for different clinical assessments, patients will be considered lost in the follow up.

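### The set called intention-to-treat is conditioned on dosing and on undefined 'evaluable' follow-up, sits badly with the planned imputation, and disagrees with the Discussion on patients found ineligible after dosing

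*Protocol article*

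**What the plan says.** Four places in the protocol article bear on who is analysed.

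- **Statistical analysis, safety set.** "All patients who receive at least one dose of randomized study drug will be included into the safety analysis".
- **Statistical analysis, main efficacy set.** This set requires a dose and something further: only a dosed patient "who has an evaluable follow-up data will be included in intention-to-treat analysis". The same paragraph then plans chained-equation multiple imputation for missing data and adds: "A complete case analysis will be presented as a sensitivity analysis". *Evaluable* is not defined.
- **Discussion.** Because history may be unavailable at enrolment, "some inclusion and exclusion criteria will be checked over the initial course of treatment, which may result in high exclusion rate of patients". On how such patients are analysed, the section is explicit: "In that case, data from those patients will be considered only for safety analysis".
- **Participants and Interventions.** When the patient cannot give a history and no suitable informant is present, "consent to participate and exclusion criteria might be confirmed within two days of protocol beginning". Interventions also allows discontinuation from the protocol "in case of screening error when including patients with history of epilepsy predicted in the study exclusion criteria", with no stated time limit and no statement of which analysis set such a patient belongs to.

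The Abstract says that analyses follow safety, intention-to-treat and efficacy concepts. The article describes no set that keeps every randomised patient.

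**The concern.** Intention-to-treat protects the randomised comparison because membership is settled at randomisation. Here membership depends on two later events: being dosed and having evaluable follow-up. The second matters more. The Introduction says that injury severity correlates with the likelihood of epilepsy, and the Discussion describes patients whose condition is often life threatening. Severity can also drive early death and loss to follow-up, and tolerability may differ by arm. If the patients who drop out of the set carry different epilepsy risks in the two arms, the primary odds ratio is biased in a direction that cannot be known beforehand.

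The set definition also determines what the imputation can do, because a patient removed from the set is not imputed. And where two sections assign the same patient to different sets, the choice could end up being made after data are seen.

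**Working it through.** **1. The plan's own figures.** The article gives 156 per group, a 15% difference (read here as absolute), two error rates (0.05 and 0.10) and 20% dropout, but no control rate. Assuming 25% versus 10% and a two-sided test, the Pocock formula gives

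n = [p1(1−p1) + p2(1−p2)] × (1.960 + 1.282)² / (p1−p2)² = (0.1875 + 0.0900) × 10.507 / 0.0225 = 129.6, so 130 per group,

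and 130 × 1.2 = 156. The stated size is therefore attainable under that assumption and is not in dispute. It is used below only as a reference case.

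**2. What each reading of *evaluable* does.**

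| Patient | Known 24-month status required | Any follow-up suffices |
|---|---|---|
| Randomised, never dosed | Out | Out |
| Dosed, no follow-up | Out | Out; not imputed; also out of complete case |
| Dosed, lost after some visits | Out; not imputed | In, and imputed |
| Dosed, 24-month status known | In | In |

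Under the first reading the set is the complete-case set for the primary outcome, so imputing that outcome is empty and the sensitivity analysis duplicates the primary one. Under the second, imputation does real work on later gaps, but neither stated efficacy analysis includes the patients with no follow-up. Under both, the undosed and the never-followed are lost.

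**3. The two sections on late ineligibility.** Take a dosed patient, followed to 24 months, in whom a disqualifying history emerges during treatment. The Statistical analysis rule places this patient in the intention-to-treat set; the Discussion allows safety only. Participants gives a two-day window for confirming exclusion criteria, the Discussion speaks of the early course of treatment, and Interventions sets no time limit for a missed history of epilepsy. The article does not say which statement governs the analysis.

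**4. Illustration of bias (all rates assumed).** Let the true risk be p in both arms, a fraction d be dropped per arm, and r be the risk among the dropped. The analysed risk is (p − d·r)/(1 − d). With p = 0.25:

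- d = 0.20, r = 0.15 in one arm: (0.25 − 0.03)/0.80 = 27.5%. r = 0.35 in the other: (0.25 − 0.07)/0.80 = 22.5%. Spurious difference: 5.0 points, one third of the 15-point design effect.
- d = 0.10, same risks: 26.1% versus 23.9%, or 2.2 points.
- Equal r in both arms: no difference at either d.

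The sign reverses if the two dropped-patient risks are swapped between arms.

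**5. Precision.** The article does not say whether the 20% allowance covers late exclusions. At the assumed 25% versus 10% (pooled two-proportion test, two-sided 5%), 156 × 0.8 = 124.8 per group has power 0.88. If a further 10% or 20% per arm move to safety only, about 112 or 100 remain, with power 0.85 or 0.80.

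**The case against.** **Imputation.** A reader might infer that the definition flatly contradicts the multiple imputation. The document does not support that without qualification. There are seven visits, and seizure data may be collected by telephone, so *evaluable* may well mean any follow-up; patients lost later would then be imputed, and complete case would be a different analysis. This objection stands. What survives is that the term is undefined and that patients with no follow-up are excluded on either reading.

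**Late ineligibility.** A reader might also infer that these exclusions break the randomised comparison. They rest largely on history that predates randomisation, participants, staff and the outcome assessor are blinded, and the two-day window in Participants closes before outcome counting starts at day 7. Such exclusions carry little bias, so this stands too. Two limits remain: the missed-epilepsy-history route has no time limit, and no rule says that eligibility is judged blind to outcome. Nor should the 48 hours in the Discussion be read as an eligibility window; it is the consent deadline. The Discussion could be read as qualifying the Statistical analysis rule, but the article does not say so.

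**Overturned result.** It is tempting to argue that the exclusions could reverse the trial's conclusion. Suppose 31 of 156 are dropped per arm and the analysed result is 31/125 on placebo versus 13/125 on biperiden (Pearson p = 0.0028). If the missing placebo patients have a 10% rate and the missing biperiden patients 25% or 40%, the full set gives 34/156 versus 21/156 (p = 0.053) or 34/156 versus 25/156 (p = 0.19). This requires the whole dropout allowance to be excluded, which the article does not say, and strongly opposite risks by arm. At 25% in both missing groups the result is 39/156 versus 21/156, p = 0.010. Imputation under missing-at-random would not correct the adverse case in any event; only a delta-adjusted analysis addresses it.

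**Visibility.** Nor would the problem be wholly hidden: mortality and serious adverse events are compared by arm, and safety covers every dosed patient. These comparisons could show unequal early death, but not its effect on the primary odds ratio.

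**Unseen plan.** A statistical analysis plan may say more. But the article itself fixes this definition, so the point is about what is stated, not about what is left out.

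**Conclusion.** The point holds in this form: the set labelled intention-to-treat is a modified set, conditioned on dosing and on undefined evaluable follow-up, and the article assigns patients found ineligible after dosing inconsistently. The follow-up condition is the main bias risk; blinded exclusions for pre-randomisation facts are a minor one.

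The document does not fix the size of the bias. In the illustration it runs from zero to 5 points in either direction, and rests on an assumed 25% risk, up to 20% dropped per arm, and assumed dropped-patient risks of 15% and 35%. This should be settled before unblinding, because it governs the primary estimate of a superiority trial.

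**What to change.** 1. Define the primary set as all randomised patients, analysed as randomised, including those never dosed.
2. Exclude only patients without consent to use their data, or with a disqualifying fact that predates randomisation and is confirmed blind to allocation and outcome. Report these exclusions by arm.
3. Apply the planned multiple imputation to patients in this set with missing epilepsy status. State how deaths before 24 months enter the primary odds ratio; the article does not say, and widening the set makes the question unavoidable.
4. Rename the present set *evaluable*, define that term, and keep the analysis as supportive.
5. Add a delta-adjusted (tipping-point) sensitivity analysis, since complete case does not probe informative loss.
6. Make Participants, Interventions, Statistical analysis and Discussion agree on the analysis set for patients found ineligible after dosing, and say whether the 20% allowance covers them. This concerns analysis membership only, not when treatment should stop.

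The cost is wording and one extra analysis.
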